### Randomization and blinding

Stratified blocked randomization is used in this study. Stratification is performed on enrolling centers and block length will be decided by an independent coder, using the software called Package for Encyclopaedia Medical Statistics 3.1 (PEMS 3.1) to generate the randomization sequence. Patients are assigned to the new tablets group, old pills group or placebo control group using a 1:1:1 ratio. The assignment for each patient is concealed in a sealed, lightproof and numbered envelope. Each envelope is assigned to a unique coded test drug package containing the specified medication according to the group assignment. For example, if a patient is assigned to the new tablets group, their unique coded test drug package will contain real *Baoji Tablets* and dummy *Baoji Pills*. Patients are randomly enrolled using the numbered envelopes and assigned to a treatment group. A blinded clinical assistant in each center performs the patient allocation. As the trial is double blinded, both investigators and patients are blinded to group assignments. The sealed envelopes are kept in locked drawers and will only be opened if there is a medical emergency.

### Interventions

#### New tablets group

Patients are administered *Baoji Tablets* 0.9 g and dummy *Baoji Pills* 3.7 g three times daily for 3 days.

#### Old pills group

Patients are administered dummy *Baoji Tablets* 0.9 g and *Baoji Pills* 3.7 g three times daily for 3 days.

#### Placebo control group

Patients are administered dummy *Baoji Tablets* 0.9 g and dummy *Baoji Pills* 3.7 g three times daily for 3 days.

All groups receive health education for the common cold, such as the recommendation to increase rest and fluid intake. During the study, patients are visited four times by the investigators. The time points for the visits are 0.5 days before baseline, at baseline, 4 days post baseline and 11 days post baseline. The follow-up visits last for one week after the treatment. Details of study visits and contents can be found in Figure 2.

**Figure 2 F2:**
[figure not shown]
Study schedule for patients.

### Outcome measurements

#### Primary outcomes

The primary outcome of this study will be the duration of all symptoms, which is defined as the number of hours from baseline to the time when the patient feels not sick at all. This can be acquired from the patient diary, in which each patient records any changes in symptoms.

#### Secondary outcomes

Secondary outcomes include duration of primary and secondary symptoms, changes in primary and secondary symptom scores and cumulative symptom score at day 4, as well as the evaluation of treatment efficacy. In this trial, the symptom score system and treatment efficacy evaluation system follow the *Guidelines for Clinical Research of New Chinese Medicine*[14]. In the symptom score system, the primary and secondary symptoms are given graded scores. The cumulative symptom score is the sum of all symptom scores. In addition, TCM signs will also be assessed (Figure 3). The treatment efficacy evaluation system uses the percentage of symptom score reduction (PSSR). The PSSR for a patient after treatment is calculated according to the following formula:

$$\mathrm{PSSR}=\left(\frac{\mathrm{Symptom}\;\mathrm{score}\;\mathrm{at}\;\mathrm{day}\;0-\mathrm{Symptom}\;\mathrm{score}\;\mathrm{at}\;\mathrm{day}\;4}{\mathrm{Symptom}\;\mathrm{score}\;\mathrm{at}\;\mathrm{day}\;0}\right)\times 100\%$$

**Figure 3 F3:**
[figure not shown]
Symptom scores and traditional Chinese medicine signs.

The symptom improvement will be classified as full recovery (PSSR ≥ 90%), good recovery (90% > PSSR ≥ 70%), modest recovery (70% > PSSR ≥ 30%) and no recovery (PSSR < 30%).

#### Safety outcomes

Safety outcomes include results of a routine blood test, routine urine test, routine stool test, fecal occult blood test, liver function test, renal function test and electrocardiogram. These biological indicators are monitored both before and after treatment. A urine pregnancy test must be done before recruiting a female patient of childbearing age.

### Data management

In our study, all data are entered electronically using Oracle Clinical Remote Data Capture. Original study forms will be kept on file at the participating sites for a period of 3 years after completion of the study. At the end of the trial, the investigators, data managers and statisticians will perform a blind review and confirm the database before processing the data. Only the principal investigator will have access to the final trial data set. All patients’ personal information is classified and is used only in this study.

### Adverse event reporting

Adverse events will be recorded in detail using medical terminology throughout the study. Severe adverse events must be reported to both the institutional review board and the principal investigator within 24 hours. If there is a medical emergency, the unblinding procedures will be initiated by the principal investigator.

### Sample size calculation and statistical analysis

The sample size was determined using PEMS 3.1 with 90% power and alpha = 0.05 (two-sided). The mean duration of all symptoms for a common cold was estimated to be 7 days with a standard deviation of 4 days [15]. To demonstrate a reduction in the duration of all symptoms by 2 days, which is defined as clinically relevant, the sample size needs to be 85 cases for each group. Considering the potential loss of patients, the number of participants recruited must be 96 per group. Therefore, a total of 288 patients will be recruited in this trial.

The statistical analysis for this study will be performed by an independent professional statistician using PEMS 3.1 in a separate location. An intent-to-treat analysis for the patients, who have received treatment at least once, will be carried out. Missing data will be adjusted using the last observation carried forward method. The per-protocol analysis will be restricted to participants who strictly follow the protocol and complete the study. The safety analysis will be conducted only for randomized subjects who have completed at least one study visit. Pearson’s chi-square test or Fisher’s exact test will be performed on categorical variables, Student’s *t*-test on continuous normally distributed variables and the Wilcoxon rank sum test on non-normal variables. Due to the multicenter design, the Cochran–Mantel–Haenszel test stratified by clinical centers and analysis of covariance adjusted for clinical center and baseline will be used in this study. The statistical significance level will be set at *P* < 0.05 and 95% confidence interval will be calculated.

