## Background

The common cold is the conventional term used to describe a mild, self-limited, viral, upper respiratory tract infection and it is the most prevalent disease experienced by humans [1]. Symptoms usually include a sore or scratchy throat, sneezing, coughing, hoarseness, runny nose, nasal obstruction and mild general symptoms like fever, headache, chills and not feeling well in general [2]. However, in clinical practice, symptoms caused by the common cold vary from person to person, and cold to cold. Well over 200 viruses are implicated in the cause of the common cold [3]. Among these pathogenic viruses, adenoviruses and enteroviruses can even cause diarrhea [4-6]. It has been reported that acute upper respiratory infection is the most common discharge diagnosis in emergency departments and the second most common diagnosis in physician offices [7,8]. In the United States, the costs associated with noninfluenza viral respiratory infections are estimated at 40 billion dollars each year, including indirect and direct costs [9]. Despite the high incidence and the economic impact of the common cold, no effective etiological treatment has been proven. Treatment thus mainly comprises symptomatic relief [10]. Although various treatments are used in clinical practice nowadays, few of them are supported by any solid evidence.

Dissatisfaction with conventional treatments offered by Western medicine has resulted in many patients seeking help from complementary and alternative medicine. Traditional Chinese medicine (TCM), a 5000-year-old ancient system of medicine, has been used to treat a wide range of diseases, including the common cold. The TCM treatment for common cold is based on the differentiation of symptoms and signs, such as fever, fatigue, headache, aversion to cold, nausea and vomiting, nasal discharge, stuffy nose, tongue proper, tongue coating and condition of pulse. With a totally different system of concepts and theories for etiology, TCM divides colds into three categories: wind-heat syndrome, wind-cold syndrome and summer-heat and dampness syndrome. Among them, the common cold with summer-heat and dampness syndrome (CCSDS) is most commonly seen in midsummer and it is primarily characterized by aversion to cold, fever, diarrhea, nausea and vomiting. According to the basic principles of TCM, CCSDS is treated by dispersing summer-heat and resolving dampness, as well as improving the spleen’s transportation function.

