### Other criteria

Participants who meet any of the following criteria are withdrawn from the study:

• Voluntarily quitting

• Misdiagnosis

• Using forbidden drugs or treatments in the course of the trial

• Patient’s actual usage of trial drug is < 80% or > 120% of the required dosage

• Unable to complete the scheduled follow-up

• The patient’s condition worsens during the study and they need hospital treatment

• The patient cannot complete the study due to adverse events or other reasons

Patients who are withdrawn are not replaced.

The whole study will be terminated or suspended early if any of the following occur:

• Serious adverse event

• Poor curative effect is found during the study

• Significant deviation from the protocol

• Flawed protocol

• The pharmaceutical supervisory and administrative department decides to terminate the study for any reason

• The sponsors decide to terminate the trial due to management or funding problems

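### Last observation carried forward is the only missing-data rule, but it does not suit a time-to-recovery primary outcome and can also mislead on the day-4 scores

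*Protocol article*

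**What the plan says.** The section on sample size and statistical analysis states: "Missing data will be adjusted using the last observation carried forward method". No outcome is exempted and no other rule is given. That section also keeps every patient who took at least one dose in the intent-to-treat analysis. It names chi-square, Fisher, t, Wilcoxon and Cochran–Mantel–Haenszel tests and analysis of covariance. None of these handles censored times.

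Under Primary outcomes, the duration of all symptoms is "the number of hours from baseline to the time when the patient feels not sick at all". Its source is the diary: "This can be acquired from the patient diary, in which each patient records any changes in symptoms".

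Under Other criteria, patients are withdrawn and not replaced for reasons that include "The patient’s condition worsens during the study and they need hospital treatment", use of forbidden drugs, adverse events and missed follow-up.

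The end of the Interventions section gives the visits: "The time points for the visits are 0.5 days before baseline, at baseline, 4 days post baseline and 11 days post baseline". Under Secondary outcomes, the percentage of symptom score reduction (PSSR) uses only the day-0 and day-4 scores, and a value below 30% falls in the lowest category, no recovery. The Background describes the illness as "a mild, self-limited, viral, upper respiratory tract infection".

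**The concern.** Carrying forward needs an earlier value of the same variable. A time to recovery has none: until the patient recovers, all that is known is that the duration exceeds the time observed. The natural way to apply the rule is to enter the time of the last diary record as the duration. A patient who worsens and is withdrawn on day 2 would then contribute one of the shortest durations in the trial.

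At day 4 the error would run the other way. If the baseline visit supplies the last score, the PSSR is 0% and the patient is classed as not recovered, in an illness that the protocol itself describes as resolving unaided. The same dropout could then count as a fast recovery on the primary outcome and as a complete failure on the secondary ones.

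The listed withdrawal reasons depend on how the patient is doing, so loss may differ between arms. Any such difference would pass directly into the treatment comparison.

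**Working it through.** **The plan's own figure.** Inputs from the sample size section: difference 2 days, SD 4, two-sided alpha 0.05, power 90%. n = 2 × (1.960 + 1.282)² × 4² / 2² = 84.06, rounded up to 85 per group. This agrees with the plan. Recruiting 96 implies an allowance of 1 − 85/96 = 11.5% loss.

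**Assumptions that are not in the documents.** Durations follow a gamma distribution with SD 4. They are capped at day 11, the last visit. Loss occurs at day 4, and a patient lost while sick is given a duration of 4 days. The loss rates are scenarios. Each calculation concerns one pair of arms with 96 patients each.

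**Error per lost patient.** With mean 7, P(T > 4) = 0.757, and the average time still to run after day 4 is 3.74 days when capped at day 11. With mean 5, the figures are 0.498 and 3.34 days. Without the cap, gamma or lognormal durations at SD 4 give 3.7 to 4.4 days.

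**Primary outcome, no true effect (mean 7 in both arms).** The false difference is the gap in loss rates × 3.74 if every lost patient is still sick. It is multiplied again by 0.757 if loss is unrelated to illness status.

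| Loss | All lost patients sick | Loss unrelated to status | Type I error |
|---|---|---|---|
| 17% v 6% | 0.11 × 3.74 = 0.41 d | × 0.757 = 0.31 d | 11–16% |
| 15% v 8% | 0.07 × 3.74 = 0.26 d | × 0.757 = 0.20 d | 7–10% |
| equal | 0 | 0 | 5% |

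Example for the error rate: the SD after capping and recoding is about 2.95, so the standard error is 2.95 × √(2/96) = 0.426. Then 0.41/0.426 = 0.96, and P(Z > 1.96 − 0.96) + P(Z < −1.96 − 0.96) is about 0.16. The arm with more loss appears to recover faster.

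**Timing of loss.** If dropout is spread evenly over days 0 to 4, without the cap, loss of 5% versus 18% gives about 0.66 days and 20% rejection.

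**Primary outcome, true 2-day effect, equal 11.5% loss.** Capping alone gives a difference of 1.82 days.
- All lost patients sick: 1.82 − 0.115 × (3.74 − 3.34) = 1.77 days.
- Loss unrelated to status: 1.82 − 0.115 × (0.757 × 3.74 − 0.498 × 3.34) = 1.69 days.

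**Day-4 recovery category.** Assume that 60% truly have good or full recovery in both arms, with 6% versus 17% of day-4 scores missing and baseline carried forward. Then 0.60 × 0.94 − 0.60 × 0.83 = 0.564 − 0.498 = 0.066, a spurious 6.6 points against the arm with more loss.

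**The case against.** The article does not say that a still-sick dropout is recorded as recovered at last contact, although a reader might infer that it does. Carrying the last status (still sick) to day 11 is another possible reading, and it would lengthen the duration. How a diary becomes a duration could also be settled in an unseen analysis plan. This stands as a limit on certainty. It does not rescue the rule, because the protocol has already fixed a method with no defined meaning for this outcome and names no test that accepts censoring.

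The day-4 part assumes that scores come only from visits. The diary records symptom changes, and the schedule and scoring figures are not shown, so interim scores may exist. They would soften the bias but not remove it, since an earlier score still ignores later natural recovery.

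The larger error rates need unequal loss. With a common loss rate of 11.5%, a gap of 11 or more patients between two arms of 96 would arise by chance only about 2% of the time. At 13% versus 10%, the false difference is about 0.1 days and type I error stays below 6%. This is fair: 17% versus 6% illustrates treatment-related loss and is not a forecast. Still, withdrawal for worsening or forbidden drugs in a placebo-controlled trial gives good reason not to assume equal loss.

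Early recovery might be thought another source of bias. It is not a listed withdrawal reason, and a patient who has recovered already has the primary event recorded.

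**Conclusion.** The concern holds. The sole missing-data rule is unsuitable for the primary outcome and should be replaced before the blind review. The size of the damage depends on the assumed loss: a false difference of 0.20 to 0.41 days and a type I error of about 7% to 16% across the two unequal-loss scenarios tabulated, and no inflation when loss is equal. With a real 2-day effect and equal loss the consequence is modest attenuation, from 1.82 to between 1.69 and 1.77 days.

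A reader might conclude that the rule favours the tablets, or that type I error will be inflated in this trial. The documents support neither. The direction depends on which arm loses more sick patients, and the documents give no loss rates by arm. The day-4 distortion is conditional on there being no interim scores.

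**What to change.** Remove last observation carried forward as the main rule and keep it at most as a labelled sensitivity analysis.

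- **Primary outcome.** Censor patients without a recorded recovery at their last diary time. Compare arms with a centre-stratified log-rank test or Cox model. Censoring assumes that loss is uninformative, which the withdrawal reasons make doubtful, so add a sensitivity analysis that treats patients withdrawn for worsening or forbidden drugs as not recovered through day 11.
- **Day-4 scores, PSSR and recovery category.** Use multiple imputation, or another model-based method, from baseline score, centre, arm and any diary data. Add a sensitivity analysis for data missing not at random.

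The cost goes beyond wording and programming. The primary test would no longer be the mean-based comparison behind the 85 per group, so the power statement needs to be restated for the new analysis. Intervals will widen slightly because the uncertainty about missing values is counted.

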**Methods/design:**

This study is designed as a multicenter, phase II, parallel-group, double-blind, double-dummy, randomized and placebo-controlled trial. A total of 288 patients will be recruited from four centers. The new tablets group are administered *Baoji Tablets* 0.9 g and dummy *Baoji Pills* 3.7 g. The old pills group are administered dummy *Baoji Tablets* 0.9 g and *Baoji Pills* 3.7 g. The placebo control group are administered dummy *Baoji Tablets* 0.9 g and dummy *Baoji Pills* 3.7 g. All drugs are taken three times daily for 3 days. The primary outcome is the duration of all symptoms. Secondary outcomes include the duration of primary and secondary symptoms, changes in primary and secondary symptom scores and cumulative symptom score at day 4, as well as an evaluation of treatment efficacy.

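### The safety set is defined by an unspecified completed visit rather than by exposure, so depending on the reading it either admits undosed patients or omits dosed patients who leave before day 4

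*Protocol article*

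**What the plan says.** The rule stands in the protocol article under Sample size calculation and statistical analysis: "The safety analysis will be conducted only for randomized subjects who have completed at least one study visit". Earlier in that paragraph the efficacy population is set by exposure: "An intent-to-treat analysis for the patients, who have received treatment at least once, will be carried out".

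The article lists four visits in the Interventions section, at the end of the placebo group text: "The time points for the visits are 0.5 days before baseline, at baseline, 4 days post baseline and 11 days post baseline". The Abstract gives the treatment course: "All drugs are taken three times daily for 3 days".

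The section Other criteria includes among its grounds for withdrawal: "The patient cannot complete the study due to adverse events or other reasons". It adds: "Patients who are withdrawn are not replaced".

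On data collection, Adverse event reporting states: "Adverse events will be recorded in detail using medical terminology throughout the study". Safety outcomes lists laboratory tests and the electrocardiogram and says: "These biological indicators are monitored both before and after treatment".

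**The concern.** A safety population should contain the people exposed to study medication. Here membership turns on attendance, and the kind of attendance is not specified. This is a rule that the article states, not a detail that it leaves out, and it differs from the exposure rule used for efficacy in the same paragraph.

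Safety is half of the trial's stated objective, and the Discussion says that the results are to inform a phase III trial. If the set depends on reaching a visit after treatment, membership can itself be affected by tolerability. An arm with more early departures for adverse events would then lose more of its events. If the set includes people who took nothing, rates are diluted. In both cases the denominator is not the exposed population.

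**Working it through.** **Inputs**

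- Visits: days -0.5, 0, 4 and 11 (Interventions).
- Dosing: 3 days from baseline (Abstract; Interventions).
- Patients per arm: 85 needed, 96 recruited (Sample size calculation and statistical analysis).
- Adverse event counts: the article gives none, so those used below are assumptions.

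**Step 1. The plan's own figure.** With a difference of 2 days, SD 4 days, two-sided alpha 0.05 and 90% power, n = 2 × (1.960 + 1.282)² × 4² / 2² = 84.1, which rounds up to 85 per group. The stated 85 is reproduced. The allowance for loss is 96 − 85 = 11 per arm, and 11/96 = 11.5%. The total is 3 × 96 = 288, as stated.

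**Step 2. Apply the rule to the schedule.** No scheduled visit lies between baseline and day 4, and the 3-day course falls wholly inside that gap. The rule therefore has two possible meanings.

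| Reading | Who is in the safety set | Dosed patients dropped | Undosed patients admitted |
|---|---|---|---|
| A: any of the four visits counts | In practice, everyone randomised | 0 | All of them |
| B: a post-baseline visit is required | Those seen at day 4 or later | Those who leave before day 4 and are not seen again | Only those who still attend |

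Under A the safety set can be larger than the dose-based intent-to-treat set. Under B it can be smaller: a patient who takes drug and leaves on day 2 with an adverse event would count for efficacy but not for safety.

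**Step 3. Size under reading B.** Let N patients be dosed and E of them have an event. Let L leave before day 4, and let k of those L have had an event. The dose-based rate is E/N and the visit-based rate is (E − k)/(N − L). The visit-based rate is too low exactly when k/L > E/N, that is, when early leavers have events more often than the arm as a whole. With N = 96, and L from 0 up to the planned allowance of 11:

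| E | L | k | Dose-based rate | Visit-based rate |
|---|---|---|---|---|
| 5 | 0 | 0 | 5/96 = 5.2% | 5/96 = 5.2% |
| 5 | 3 | 1 | 5/96 = 5.2% | 4/93 = 4.3% |
| 5 | 3 | 3 | 5/96 = 5.2% | 2/93 = 2.2% |
| 10 | 11 | 0 | 10/96 = 10.4% | 10/85 = 11.8% |
| 10 | 11 | 1 | 10/96 = 10.4% | 9/85 = 10.6% |
| 10 | 11 | 3 | 10/96 = 10.4% | 7/85 = 8.2% |

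The error is zero when nobody leaves early. It can be slightly upward when the leavers had few events, and it is downward when departure is linked to adverse events.

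**Step 4. Size under reading A.** No event in a dosed patient is lost. With m undosed patients among 96 randomised, the rate becomes E/96 instead of E/(96 − m). The article gives no value for m. Assuming m = 3 and E = 10, 10/93 = 10.8% becomes 10/96 = 10.4%, a small dilution.

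**The case against.** The strongest reply is that the article itself counts the visits at day -0.5 and baseline among the four. On those words a randomised patient has normally completed a visit before the first dose, so no dosed patient is lost. Nothing in the safety sentence mentions day 4 or a post-baseline visit. This stands. A reader might infer that the plan excludes patients who stop early because of adverse events, but the article does not say so. The restrictive word at the start of the rule makes a post-baseline reading plausible, since under reading A nothing is restricted; it does not establish that reading.

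Second, withdrawal is not the same as missing the day-4 visit. The article does not say when patients withdrawn for adverse events leave, or whether they are still seen at day 4. This also stands, and it is why the range in the working starts at zero.

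Third, the 11 per arm is a planning allowance with no split by cause or timing. A more dramatic illustration is easy to build. If all 11 are lost before day 4, 6 of them with an event, and 6 completers also have events, 12/96 = 12.5% is reported as 6/85 = 7.1%. The arithmetic is right, but none of those event counts or timings is in the article, so it should not be read as the expected size.

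Fourth, the listed safety outcomes are laboratory tests and the electrocardiogram, and a patient without a post-treatment value contributes no change on them whatever the set. That is correct for those measures. It does not cover adverse events, which are recorded throughout the study and need no visit to be counted.

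Finally, an unseen full protocol or analysis plan may define the visit. It may, but the sentence as published fixes attendance, not exposure, as the criterion, and a clearer visit definition would not change that.

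**Conclusion.** The point holds in conditional form. The safety set rests on attendance, the qualifying visit is not specified, and neither reading gives the exposed population. Under reading A the fault is limited to undosed patients entering the denominator; their number is unknown, and nothing in the article suggests that it is large. Under reading B, 0 to 11 of 96 dosed patients per arm drop out of the safety set if the planned allowance is taken as the upper bound. Adverse event rates are then understated whenever early departure is linked to events. The illustrated rates rest on assumed counts.

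Severity is moderate: safety is a stated objective and the defect touches its denominator, but the harm depends on a reading that the article leaves open. Confidence is moderate for the same reason.

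**What to change.** Replace the safety sentence with a dose-based definition: all randomised patients who took at least one dose of study medication. State that every adverse event from the first dose is counted, whether or not the patient completed a later visit. Summarise laboratory and electrocardiogram changes for the members of that set who have a post-treatment value, and give their number.

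The cost is one sentence of definition and its consequence for the tables. No new data are needed, because adverse events are already to be recorded throughout. The trial is still recruiting, so the change can be made before the planned blind review and confirmation of the database.

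### Read literally, the rule for categorical variables sends the four ordered recovery classes, a secondary outcome, to a test that ignores their order

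*Protocol article*

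**What the plan says.** Under Secondary outcomes, the protocol article lists an evaluation of treatment efficacy after the symptom durations and symptom scores. It rests on the percentage of symptom score reduction (PSSR) from day 0 to day 4, cut at 90%, 70% and 30%. The top two classes are full and good recovery, and the lower two are given as "modest recovery (70% > PSSR ≥ 30%) and no recovery (PSSR < 30" per cent. Of the listed efficacy outcomes, this is the only one defined as categories.

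The section on sample size and statistical analysis sets tests by type of variable. For categorical data, Pearson's chi-square or Fisher's "exact test will be performed on categorical variables". A t-test is given for normally distributed continuous variables and a Wilcoxon rank sum test for non-normal ones. The section then adds a Cochran-Mantel-Haenszel test stratified by center and an analysis of covariance. It does not name the recovery classes, has no separate rule for ordinal variables, and does not say which form of the Cochran-Mantel-Haenszel test is meant or for which outcome.

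**The concern.** Pearson's and Fisher's tests give the same p-value if the four class labels are shuffled. They ask whether the class distributions differ, not whether recovery is better. A significant result could therefore arise without any shift toward recovery. When there is a consistent shift, the test spreads its power over 3 degrees of freedom in a two-arm comparison, where a test that uses the order spends 1.

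The stated hypothesis is directional (shorter symptoms with the new tablets), and the trial is meant to support a phase III study. An efficacy grading read without its order serves both aims poorly. What is at stake is the precision and interpretability of one secondary outcome.

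**Working it through.** **1. The plan's own figure.** The sample size concerns the primary outcome, with two-sided alpha 0.05 and 90% power. The duration is "estimated to be 7 days with a standard deviation of 4 days", and the target is "a reduction in the duration of all symptoms by 2 days, which is defined as clinically relevant".

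n = 2 × (1.960 + 1.2816)² × 4² / 2² = 2 × 10.507 × 4 = 84.06, rounded up to 85.

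This agrees with "the sample size needs to be 85 cases for each group"; exact t-test power at 85 is 0.900. Allowing for loss, "the number of participants recruited must be 96 per group", which implies a loss of 1 − 85/96 = 11.5%, and 3 × 96 = 288. The figure reproduces. It does not involve the recovery classes, for which the documents give no power, expected distribution or effect.

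**2. Assumptions for the recovery classes.** All are mine, because the documents give none:
- two arms compared at a time, 85 per arm, two-sided 0.05;
- control splits (full/good/modest/none, in %) of 25/25/25/25, 20/30/35/15, 10/25/40/25 and 40/30/20/10;
- a common odds ratio of 1.5 to 3.0 toward recovery.

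Example with equal control classes and odds ratio 2.0: the cumulative control proportions 0.25, 0.50, 0.75 have odds 1/3, 1, 3. Doubled, these are 2/3, 2, 6, so the cumulative proportions become 0.400, 0.667, 0.857 and the classes 0.400, 0.267, 0.190, 0.143.

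**3. Power.** Simulation with 20,000 runs per scenario: Pearson's chi-square (3 df) against the tie-corrected Wilcoxon rank sum test. Ranges are over the four control splits.

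| Common odds ratio | Pearson | Rank test | Loss (points) |
|---|---|---|---|
| 1.0 (no effect) | 0.05 | 0.05 | none |
| 1.5 | 0.19–0.20 | 0.30–0.32 | 10–11 |
| 2.0 | 0.50–0.53 | 0.67–0.70 | 17–18 |
| 2.5 | 0.75–0.79 | 0.88–0.90 | 11–13 |
| 3.0 | 0.89–0.92 | 0.96–0.98 | 5–7 |

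For the equal split at odds ratio 2.0 the pair is 0.53 against 0.70. At 96 per arm and odds ratio 2.0 the ranges are 0.55–0.59 against 0.72–0.76.

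**4. A different assumed model.** Take a placebo split of 25/30/30/15 (none/modest/good/full) and a normal latent shift of 0.45 SD. The cutpoints −0.674, 0.126, 1.036 move down by 0.45, which gives 0.130/0.242/0.348/0.279. Power at 85 per arm is 0.62 with Pearson and 0.78 with the rank test.

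**5. Cross-check by noncentral chi-square.** The noncentrality needed for 80% power is 7.849 on 1 df and 10.903 on 3 df, a ratio of 1.39. For 90% it is 10.507 and 14.171, a ratio of 1.35. For an ordered shift the unordered test thus needs about 35–39% more patients for equal power.

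**6. When the order does not help.** With 25/25/25/25 against 40/10/25/25 (full/good/modest/none) at 85 per arm, power is about 0.70 with Pearson and 0.15 with the rank test.

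**The case against.** The strongest reply is that the plan never assigns a test to the recovery classes. The statistical section is a short list by type of variable, and a rank test and a center-stratified Cochran-Mantel-Haenszel test stand in the same paragraph. Either could serve, and matching outcomes to tests is commonly left to an analysis plan that is not shown. This stands in part. A reader might infer that the protocol has assigned the classes to an unordered test; the text does not go that far. But the point is not a silence. The document states a rule for categorical variables, and these classes are categorical. The Wilcoxon test follows directly on the t-test for continuous data, so its natural scope is continuous variables that are not normal. The general-association form of the Cochran-Mantel-Haenszel test also ignores order.

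A reader might also infer that the unordered test has nothing in its favor. That is wrong: it detects non-monotone differences that a rank test misses, as step 6 shows. An efficacy grading is not meant to detect such patterns, but the trade should be stated.

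Finally, this is one secondary outcome, and the symptom scores behind PSSR are secondary outcomes in their own right, with analysis of covariance provided. The graded information is therefore not lost to the trial. That stands and limits the importance.

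**Conclusion.** The point holds as a minor matter of analysis choice. Taken at its word, the general rule gives an ordered secondary outcome a test that ignores the order, and nothing else in the section clearly redirects it.

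Under a consistent shift toward recovery the cost is about 10 to 18 points of power at moderate effects and 5 to 7 points at an odds ratio of 3.0. These figures rest wholly on assumed class distributions and effects, and on pairwise comparison. The trial has three arms (the new tablets group, "old pills group or placebo control group using a 1:1:1 ratio"), and the section does not say whether the classes are compared pairwise or across all arms.

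The documents do not support reading this as a threat to validity or as an underpowered trial. Both tests hold type I error at about 0.05, and the primary outcome and the 85 per group are untouched.

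**What to change.** State that the four recovery classes are analysed with the Cochran-Mantel-Haenszel row-mean-score test stratified by center (the van Elteren test when within-center modified ridit scores are used), and that Pearson's and Fisher's tests are kept for unordered variables. A center-adjusted common odds ratio with a 95% confidence interval may be added as the estimate; it is optional, because it brings its own proportional-odds assumption.

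The cost is one sentence, with the same data and patients and a test family that the plan already names. The article reports that recruitment is ongoing and that a blind review precedes data processing, so the choice can be fixed before unblinding. The one statistical cost is lower power for non-monotone differences between arms.
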